#### Model development, apparent performance assessment and internal validation

The predictors of adverse maternal outcomes will be identified to develop and externally validate a simple, interpretable and clinically applicable prediction model with face validity. We will use a transparent process that implements appropriate statistical methods and adheres to current methodological recommendations.

A backwards selection procedure will be used to decide which of the candidate predictor variables should be included in the final prediction model (with *p* < 0.15 taken conservatively to warrant inclusion). Continuous variables will be kept as continuous in the model (rather than dichotomising), to avoid a loss of power [27, 28]. Non-linear trends will also be considered using the multivariable fractional polynomial procedure [29, 30], which uses multivariable models to eliminate weaker predictors and identify transformations of continuous predictors that best predict outcome. Large amounts of missing variable data are not expected, but some will inevitably occur, with not all patients providing all variables of interest. Multiple imputation will be used to impute, with 5 imputations, under a missing at random assumption, missing values so as to avoid excluding patients from the analysis [27].

For survival analysis, failure event is defined as an adverse outcome or delivery occurring before 34 weeks of gestation. We will use a flexible parametric survival model via the Royston-Parmar approach [31–33], with the cumulative baseline hazard scale modelled using restricted cubic splines. The number of knots will be chosen by visual inspection. For the binary adverse maternal outcome by discharge, a logistic regression-modelling framework will be undertaken with the logit probability of an adverse outcome being the response variable.

We will assess the apparent performance of the fitted models for discrimination using the *C*-statistic (Harrell’s *C*-statistic from the survival model and AUC from the logistic model), with 95% confidence interval, averaging across the same imputed datasets that were used to generate the model. A *C*-statistic close to 1 indicates excellent discrimination and 0.5 indicates no discrimination beyond chance. The calibration performance of the model (fit of observed to expected risk across all individuals) will be assessed by checking whether the calibration slope is 1. As the model will be developed in the same data, perfect agreement is expected on average across the imputed datasets.

Non-parametric bootstrapping will be used to internally validate and examine the potential for overfitting of our developed models, by repeating the variable selection procedure in 100 bootstrap datasets from each of the 5 multiple imputation datasets, providing a total of 500 datasets. This leads to a new final model being produced in each of the bootstrap samples. We will average the difference in the performance of the models to obtain a single estimate of optimism for the *C*-statistic and the calibration slope. The optimism-adjusted performance statistics will be obtained by subtracting the above estimate of optimism from the original apparent performance statistics. The optimism-adjusted calibration slope will be taken as the uniform shrinkage, and the final models will be corrected by this shrinkage factor.

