### Sample size considerations

From our systematic reviews [17], 20% of women with early-onset pre-eclampsia are expected to have adverse maternal outcomes at any time before discharge. Rules of thumb for fitting multivariate models suggest about 10 events for every variable are required to reduce issues with overfitting, and we will work within this constraint [24–26]. We initially planned to examine 10 predictor variables and hence planned to recruit 500 women. However, the event rate was lower than predicted, so we revised our plan to recruit sufficient women to obtain 100 events. Subsequent to the inclusion of delivery before 34 weeks as a component of the composite outcome, we revised our plan to include 22 candidate predictor variables, which was approved by the independent study Committees.

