## Discussion

Pre-eclampsia and its complications are still considered to be one of the leading causes of maternal and fetal morbidity and mortality; the condition utilises a large proportion of NHS resources. Accurate prediction and early management can significantly improve these outcomes. However, clinicians and policymakers currently do not have the evidence on which they can base their recommendations.

Timely prediction of complications in women with early-onset pre-eclampsia involves the use of a combination of maternal characteristics, symptoms, physical signs and investigations [21]. These ‘tests’ are to some extent haphazardly performed in all units, due to the absence of a structured approach. The most important determinant of perinatal outcome is gestational age, with more than half the chance of intact fetal survival when this is more than 27 weeks and the birth weight is more than 600 g [34].

A recent Cochrane review [10] has shown that expectant management reduced risk of fetal and neonatal complications without increase in maternal complications. Clinicians are reluctant to promote expectant management due to uncertainties around the scale of maternal risk. One of the main reasons for this lack of confidence in applying risk scores in practice is the absence of sufficient evidence to show the reproducibility and transportability of the model in a different population [11]. A good performing prediction model is one that is accurate, validated in populations and datasets external to those used to develop the model, widely applicable in practice, and acceptable to patients and ultimately improves clinical outcomes by helping clinicians and patients make more informed decisions. With very small numbers of cases and events per variable, early-onset pre-eclampsia contributed little to current published models [8, 35, 36].

It is currently difficult to identify those mothers with early-onset pre-eclampsia who are at increased risk of developing complications, and this risk cannot be graded. There is a need for a prognostic model to include the predictive role of more than one test results on the outcome with individualised risk assessment. Provision of individualised risk estimates for adverse maternal outcomes through the PREP study will help clinicians make suitable decisions after discussion with the parents.

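### Five imputations are fixed in advance, with no link to the missingness found, while 22 candidate predictors face keep/drop decisions at p < 0.15; borderline predictors can change status with the imputation seed

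*Protocol article*

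**What the plan says.** The section on model development, apparent performance assessment and internal validation in the protocol article fixes the number of imputations: "Multiple imputation will be used to impute, with 5 imputations, under a missing at random assumption". On the amount of missing data it says only this: "Large amounts of missing variable data are not expected, but some will inevitably occur". It gives no rate, and on which predictors will have gaps it offers no more than "with not all patients providing all variables of interest".

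The same section sets the selection rule: "A backwards selection procedure will be used to decide which of the candidate predictor variables should be included in the final prediction model". Fractional polynomials are also considered. The threshold for keeping a predictor is a p-value under "0.15 taken conservatively to warrant inclusion". Under Sample size considerations the number of candidates is raised: "we revised our plan to include 22 candidate predictor variables". Table 2 agrees with that count for the maternal models: 3 maternal characteristics, 1 history score, 3 symptom items, 6 bedside items, 7 laboratory tests and 2 management items, and 3 + 1 + 3 + 6 + 7 + 2 = 22.

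Internal validation builds on the five datasets: 100 bootstrap samples from each, 500 in all, with selection repeated in every one. So the number of imputations is a stated choice in this article and has not been left to the analysis plan.

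**The concern.** A small number of imputations costs little precision when the aim is to estimate a coefficient. Here the pooled results also decide which predictors enter the published equation, by comparing a p-value with 0.15. A p-value pooled over five imputed datasets carries random error from the imputation itself. A predictor near the threshold can therefore be kept under one random seed and dropped under another, with the same women and the same data.

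The number was chosen before the missingness was known, and nothing in the text adjusts it afterwards. What is at stake is the reproducibility of the borderline part of the variable list in both the survival and the logistic model.

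**Working it through.** **Inputs from the protocol article.** Imputations m = 5; 22 candidates; threshold p < 0.15; 100 bootstrap samples per imputed dataset. The stated bootstrap total reproduces: 100 × 5 = 500. No figure is given to support m = 5, so there is none to reproduce for that choice.

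**Inputs that must be assumed.** The missingness per predictor, and the fraction of missing information (FMI) of a coefficient. Neither is in the document, so ranges are shown. The calculations also assume selection on tests pooled by Rubin's rules; the article does not say how selection is combined across imputed datasets, which an analysis plan may settle.

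**1. Share of women with a gap.** If k predictors are each missing independently at rate q, the share with at least one gap is 1 − (1 − q)^k.

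| q | all 22 incomplete | 10 incomplete |
|---|---|---|
| 1% | 20% | 10% |
| 2% | 36% | 18% |
| 5% | 68% | 40% |

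The 10 items are the seven laboratory tests plus clonus, reflexes and oxygen saturation. Gaps that cluster in the same women would lower these shares.

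**2. Loss of efficiency.** Relative efficiency is 1/(1 + FMI/m). With m = 5 it is 0.990 at FMI 0.05, 0.980 at 0.10 and 0.943 at 0.30. On this measure five is adequate at low missingness.

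**3. Noise in the p-value.** In units of its standard error, the pooled estimate varies between seeds with standard deviation √(FMI/m). A two-sided p of 0.15 corresponds to z = 1.44.

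- FMI 0.05, m = 5: √(0.05/5) = 0.100; z runs over 1.44 ± 1.96 × 0.100, or 1.24 to 1.64; p runs from 0.10 to 0.21.
- FMI 0.10, m = 5: √(0.10/5) = 0.141; z runs from 1.16 to 1.72; p runs from 0.09 to 0.25.

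Allowing also for variation in the estimated between-imputation variance, with the t reference distribution, gives 0.102 to 0.219 and 0.085 to 0.259. At FMI 0.30 the same calculation gives 0.047 to 0.386. With m = 20 the ranges at FMI 0.05 and 0.10 shrink to about 0.12 to 0.18 and 0.11 to 0.20.

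**4. Which FMI goes with which missingness.** In a simulation (assumed: n = 500, 22 normal predictors with correlation 0.2, all 22 missing completely at random, chained imputation, logistic outcome), mean FMI was 0.014, 0.029, 0.071, 0.143 and 0.277 at 1%, 2%, 5%, 10% and 20% missing per predictor. FMI of 0.20 or more therefore needs more than 10% missing per predictor.

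**5. Chance that a predictor changes status between two seeds.**

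| p with unlimited imputations | m | FMI 0.05 | FMI 0.10 | FMI 0.20 | FMI 0.30 |
|---|---|---|---|---|---|
| 0.05 | 5 | 0.000 | 0.003 | 0.055 | 0.152 |
| 0.10 | 5 | 0.061 | 0.205 | 0.365 | 0.434 |
| 0.10 | 20 | 0.000 | 0.007 | 0.078 | 0.170 |

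A predictor sitting exactly at 0.15 changes about half the time whatever m is.

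**6. Whole list.** In the simulation of step 4, the probability that two seeds select different lists was:

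| missing per predictor | m = 5 | m = 20 | m = 50 |
|---|---|---|---|
| 1% | 0.32 | 0.20 | 0.17 |
| 2% | 0.29 | 0.12 | 0.08 |
| 5% | 0.56 | 0.23 | 0.25 |
| 10% | 0.63 | 0.50 | 0.17 |

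With m = 5 the lists differed by about 0.5 variables on average at 1–2% missing and 1.1–1.2 at 5–10%. These are coarse figures from 12 simulated datasets per rate; small reversals between neighbouring cells are noise. They depend on the assumed effects, and on granting gaps in all 22 predictors.

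**The case against.** The best defence is that five imputations suit the little missing data the authors expect ("Large amounts of missing variable data are not expected"). The section on study design and conduct describes the predictors as routine care, and several candidates (age, gestation, number of fetuses, blood pressure, and usually a proteinuria measure) are tied to eligibility or consent and should rarely be missing. This stands. At an FMI of 0.05 or less the efficiency loss is 1% or less, and only predictors near the threshold are at risk.

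A reader might infer that all 22 predictors will be incompletely recorded, because the Discussion says the tests "are to some extent haphazardly performed in all units, due to the absence of a structured approach". The document does not support that: the phrase is qualified, describes current practice as motivation for the study, and forecasts nothing about the cohort.

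A reader might also put the share of incomplete women in step 1 beside the p-value ranges at FMI 0.20 to 0.30. These do not belong together: 1–5% missing per predictor gave a mean FMI of only 0.014 to 0.071.

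Finally, selection is repeated in 500 bootstrap samples, the final model is shrunk, and two external cohorts follow. Selection instability is thus carried into the optimism estimate, which limits the harm. It does not settle which variables are published, and the bootstrap reuses the same five imputed datasets. No calculation here shows a material error in the C-statistic or the optimism estimate, so that is not claimed.

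**Conclusion.** The point holds in a conditional form. Five imputations are specified without a rationale and without a link to the missingness observed, in a plan whose variable list rests on a p-value threshold. At an FMI of 0.05 to 0.10, which the simulation places at roughly 5% missing or somewhat more in every predictor, borderline predictors can move in or out between seeds. Predictors with p of 0.05 or below almost never do at that level.

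It does not follow that five is too few whatever the data show, or that the final list is bound to depend on the seed. The first needs a missingness rate that the document does not give. The second is a probability, about 0.3 at 1–2% missing per predictor and about 0.6 at 5–10% even when all 22 are assumed incomplete, and some of it remains with 50 imputations.

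This is a minor to moderate point. It is worth acting on because the remedy is nearly free. The size rests on the assumed FMI values, pooled selection tests and the simulation settings above.

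**What to change.** Replace the fixed five with a rule: the number of imputations is at least the observed percentage of women with any missing candidate predictor, and never below 20. If half the women had a gap, this would mean 50. This is a working convention and is not derived from the document.

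Keep the bootstrap total near 500 by taking fewer resamples per imputed dataset: 25 each with 20 imputations (25 × 20 = 500), or 10 each with 50 (10 × 50 = 500).

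Repeat the imputation and selection under a second seed, and report any predictor whose status changes. A change would mark that predictor as borderline; it would not invalidate the model.

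The cost is computing time. Recruitment, data collection and clinical conduct are unaffected.

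### The 95% confidence interval for discrimination is attached to the apparent C-statistic and so is centred too high; it belongs on the optimism-adjusted C

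*Protocol article*

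**What the plan says.** All of this is in the Protocol article. Except where noted, it is in the section on model development, apparent performance assessment and internal validation.

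- **Selection.** "A backwards selection procedure will be used to decide which of the candidate predictor variables should be included in the final prediction model"; the threshold for retention is p < 0.15, with fractional polynomials for continuous variables. On the number of candidates, the sample size section says: "we revised our plan to include 22 candidate predictor variables".
- **Interval.** "We will assess the apparent performance of the fitted models for discrimination" by Harrell's C for the survival model and the "AUC from the logistic model), with 95% confidence interval, averaging across the same imputed datasets that were used to generate the model".
- **Scale.** The text explains that "0.5 indicates no discrimination beyond chance".
- **Correction.** Selection is repeated in 100 bootstrap samples from each of 5 imputed datasets. The results are averaged to one optimism figure for the C-statistic and one for the calibration slope. "The optimism-adjusted performance statistics will be obtained by subtracting the above estimate of optimism from the original apparent performance statistics".

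The apparent C is the only discrimination statistic to which the article gives a confidence interval.

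**The concern.** A standard interval for a C-statistic describes sampling error for a score settled before the data were seen. Here the choice of predictors, their transformations and their coefficients all come from the women in whom the C is then computed. The apparent C is therefore too high on average, and an interval built round it inherits that displacement. The plan recognises the problem for the point estimate and subtracts the optimism, but it leaves the interval on the uncorrected value.

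Internal validation is part of the primary objective. A reader who sets the adjusted C beside the stated interval will take from it both a location that is too favourable and a coverage that it does not have.

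**Working it through.** **1. Inputs.** From the article: 22 candidates, retention at p < 0.15, a two-sided 95% interval on the apparent C, about 10 events per candidate, and a 20% planning event rate. Assumed: the final numbers of women and events, a DeLong interval (no method is named), linear terms, complete data, and independent standard-normal candidates except where stated.

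**2. The plan's own figure.** 10 candidates × 10 events = 100 events, and 100 / 0.20 = 500 women, which matches the article. For the present 22 candidates the same rule gives 22 × 10 = 220 events, or 220 / 0.20 = 1,100 women. Delivery before 34 weeks now counts as an event, so a higher rate is plausible. As a second case take 800 women at an assumed 60%: 800 × 0.60 = 480 events, and 480 / 22 = 21.8 per candidate.

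**3. Why selection matters.** If no candidate predicts anything, about 22 × 0.15 = 3.3 are kept. Treating the tests as independent, the chance of keeping at least one is 1 − 0.85^22 = 1 − 0.028 = 97.2%.

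**4. Coverage with real signal.** Logistic model, backward elimination at p < 0.15, 300 datasets per row. The true C of each selected model was measured in 40,000 new women. The last column subtracts from both limits the optimism from 25 bootstrap repeats of the selection (first 150 datasets).

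| Assumed size | Real predictors | Interval on apparent C covers true C | After shifting both limits |
|---|---|---|---|
| 1,100 women / 220 events | 6, log-OR 0.3 (best C about 0.69) | 73.7% | 90.0% |
| 1,100 / 220 | 8, log-OR 0.5 (best C about 0.82) | 88.0% | 90.7% |
| 800 / 480 | 6, log-OR 0.3 | 64.0% | 89.3% |
| 800 / 480 | 8, log-OR 0.5 | 83.0% | 90.7% |

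Monte Carlo standard errors are about √(0.737 × 0.263 / 300) = 0.025 for the third column and √(0.90 × 0.10 / 150) = 0.024 for the fourth. With a further simulation at 220 to 480 events, the ranges become roughly 59 to 88% before the shift and about 87 to 92% after it.

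**5. Direction of the misses.** In a companion simulation 5 of the 22 candidates were real, with 1,000 women and 600 events (300 datasets per row):

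| log-OR | Mean apparent C | Mean true C | Gap | Coverage | Lower limit above true C |
|---|---|---|---|---|---|
| 0.20 | 0.638 | 0.604 | 0.034 | 49.7% | 50.3% |
| 0.35 | 0.710 | 0.690 | 0.020 | 79.7% | 20.3% |
| 0.50 | 0.767 | 0.756 | 0.011 | 85.7% | 13.7% |

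In the first two rows every miss lies above the truth (49.7 + 50.3 = 100; 79.7 + 20.3 = 100). In the third, 13.7 of 14.3 percentage points do. The first row also shows that weak signal can take coverage below the range in step 4, even with many events.

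A smaller run at this size (80 datasets, log-OR 0.35) confirms that the centre is the main fault. Subtracting optimism moved the mean C from 0.708 to 0.682, against a true 0.686, and coverage rose from 70% to 90%.

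**6. Stress case.** With 22 pure-noise candidates the apparent interval lies wholly above 0.5 in 89.3% of datasets (1,100 / 220) and 87.0% (800 / 480). A survival analogue, using Cox backward elimination as a stand-in for the Royston-Parmar model and Harrell's C, gave 88.5 to 91.7% at assumed sizes of 500 to 1,000 women and 100 to 300 events. With 10 candidates (logistic model) the figure is 56.2%.

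**The case against.** The strongest reply is that the plan already deals with optimism. It calls the statistic apparent, repeats the whole selection in 500 bootstrap datasets, subtracts the optimism, shrinks the model, and plans validation in two outside cohorts. Its Discussion says that good performance in the development data is not enough, even after internal validation. If the apparent C, its interval and the optimism are all published, a reader can shift the limits unaided. All of this stands, and it makes the point minor. It does not repair the interval, because the correction is written for the point estimate only.

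Four stronger readings are tempting, and the article does not support them:

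- **A test against 0.5.** A reader might infer one because the value appears right after the interval. The sentence only explains the scale, and no decision depends on excluding 0.5. The candidates were also picked in advance as promising from systematic reviews, so pure noise is a stress case and not a picture of this study.
- **22 candidates on 100 events.** That is 100 / 22 = 4.5 events per candidate and would make coverage look much worse. But "so we revised our plan to recruit sufficient women to obtain 100 events" belongs to the stage with 10 candidates. The 22 came after the composite was widened, and the article says it will respect the 10-per-variable rule.
- **Lost between-imputation variance.** Averaging across imputed datasets need not mean averaging interval limits. It is compatible with Rubin's rules.
- **No interval at all for the adjusted C.** The article is silent, and a fuller plan may supply one. The point rests on where the article does place the interval.

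**Conclusion.** The point holds as a minor one. The interval that the article specifies is for a statistic that the plan itself goes on to correct as too high. At about 10 or more events per candidate it covers the selected model's true C in roughly 59 to 88% of simulated datasets, not 95%, and it errs almost always on the favourable side.

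These figures rest on assumed sample sizes and effect sizes, a DeLong-type interval, linear terms and complete data. Fractional polynomials and imputation were not simulated; a wider search would be expected to add optimism. Coverage with real signal was simulated for the logistic model only. For Harrell's C the evidence is the stress case, so the conclusion there rests on the same mechanism and not on a coverage figure. No selection step, shrinkage factor or validation step is called into question.

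**What to change.** In the section on model development, apparent performance assessment and internal validation, move the 95% confidence interval from the apparent to the optimism-adjusted C-statistic, for both Harrell's C and the AUC, and present the apparent C as descriptive only.

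- **Minimum.** Subtract the bootstrap optimism from both limits. This uses the 500 bootstrap datasets already planned and needs one sentence. Coverage with real signal is then about 87 to 92%, still somewhat short of 95%, because the shift ignores the uncertainty of the selection and of the optimism estimate. The article should say so.
- **Fuller version.** Use a bootstrap interval that repeats both the selection and the optimism correction within each outer sample. This would carry the selection uncertainty too, at the price of computing time. Its coverage was not simulated here.

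No new data are needed. The downside is presentational: the reported interval moves down, and with the fuller version it is also wider.
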